### Secondary outcome measures

Changes in the levels of plasma inflammatory factors such as IL-6, IL-8, IL-10, IL-1β, and TNF-α [time frame: up to 3 days]Changes of plasma MIF levels during the perioperative period [time frame: up to 3 days]Changes of plasma CRP levels during the perioperative period [time frame: up to 3 days]Changes of the plasma II, VII, IX, X, XI, and XII levels during the perioperative period [time frame: 2 days]Changes of the plasma APTT, PT, FIB, FDP, and DDi levels during the perioperative period [time frame: 3 days]Total drainage within the first 24 h of surgery [time frame: 24 h]Incidence of postoperative acute kidney injury [time frame: up to 30 days]: increase in serum creatinine ≥ 150% or ≥ 26.5 μmol/l from baseline [13]Incidence of postoperative respiratory failure [time frame: up to 30 days]: uninterrupted postoperative mechanical ventilation for more than 48 h [10]Incidence of postoperative delirium [time frame: up to 30 days]: we will assess delirium once a day for a total of 3 times during the first 72 h after ICU admission, using standard delirium assessments (CAM or CAM-ICU). Before the CAM-ICU will be performed, a Richmond Agitation Sedation Scale (RASS) sore should be evaluated in advance [21]Incidence of postoperative liver injury [time frame: up to 30 days]: ALT level above 150 U/l [22]Incidence of postoperative myocardial infarction [time frame: up to 30 days]: a rise and/or fall of cTn values with at least 1 value above the 99th percentile upper reference limit and at least 1 of the following:
Symptoms of myocardial ischemiaNew ischemic ECG changesDevelopment of pathological Q wavesImaging evidence of new loss of viable myocardium or new regional wall motion abnormality in a pattern consistent with an ischemic etiologyIdentification of a coronary thrombus by angiography or autopsy (not for types 2 or 3 MIs) [23]

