### Objective and hypothesis

This study is a single-center, randomized, controlled, double-blind clinical trial. Subjects undergoing DHCA/CPB will be allocated to the hemoperfusion group and control group. The main purpose of this study is to determine if the levels of pro-inflammatory cytokines and anti-inflammatory cytokines differ between the two study groups in the perioperative period. In addition, differences in perioperative coagulation parameters, blood product usages in the intensive care unit (ICU), length of hospital stay, postoperative complications, and all-cause mortality between two groups will also be determined. We hypothesize that hemoperfusion could improve the overall prognosis in patients with acute type A aortic dissection undergoing cardiopulmonary bypass and DHCA.

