### Blood sample collection and detection

During the perioperative period, plasma inflammatory factors levels will be measured at the following time points: before operation (T0), CPB initiation (T1), lowest intraoperative temperature (T2), end of CPB (T3), end of the operation (T4), 24 h after completion of the procedure (T5), 48 h after completion of the procedure (T6), and 72 h after completion of the procedure (T7).

Parameters of coagulation including plasma-activated partial thromboplastin time (APTT), prothrombin time (PT), fibrinogen (FIB), fibrinogen degradation product (FDP), and d-dimer (DDi) levels will be measured at the following time points: before operation, 24 h after completion of the procedure (POD 1), 48 h after completion of the procedure (POD 2), and 72 h after completion of the procedure (POD 3).

Similarly, levels of coagulation factors including II, VII, IX, X, XI, and XII will be measured at the following time points: before operation, end of CPB, end of the operation, 24 h after completion of the procedure (POD 1), and 48 h after completion of the procedure (POD 2).

Measurement of inflammatory cytokines levels: blood samples are collected through radial artery catheterization. The first 5 ml will be discarded when sampling. Following collection, blood samples are immediately centrifuged at 3000 rpm for 15 min at 4 °C. The plasma yielded will be stored in the − 80 °C refrigerator till the time of measurements. Enzyme-linked immunosorbent assay (ELISA) is used for the measurement of inflammatory cytokines.

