### Data analysis

After completion of the trial, data analysis will be done by a certified statistician with SPSS20.0 (IBM, Chicago, IL, USA). Levels of inflammatory cytokines and coagulation parameters will be expressed as mean ± standard deviation or median (interquartile range). An independent *t* test or the Wilcoxon signed-rank test will be used to check if the data is within normal distribution before analysis. Categorical variables will be analyzed with chi-squared and Fisher’s exact tests.

The relative risk of primary and secondary outcomes in the hemoperfusion group and the control group will be compared using the multivariate logistic regression. Kaplan-Meier curves and log-rank analysis will be used to compare inter-group differences in primary and secondary outcomes. When comparing the changes in coagulation factor levels during the perioperative period, the effect of hemoperfusion on coagulation factors throughout the study will be assessed using repeated measures’ analysis of variance (ANOVA) and analysis of covariance (ANCOVA). When the *p* < 0.05, the result is considered statistically significant.

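### Cytokine and clotting-test outcomes are defined as changes but discussed as levels, and the only longitudinal analysis stated covers coagulation factors, with no stated use of the preoperative value for the other markers

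*Protocol article*

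**What the plan says.** *Outcomes.* Secondary outcome measures words three groups of serial laboratory markers as changes. For the inflammatory markers it has "Changes in the levels of plasma inflammatory factors such as IL-6, IL-8, IL-10, IL-1β, and TNF-α", with separate items in the same form for MIF and CRP. For the clotting tests it has "Changes of the plasma APTT, PT, FIB, FDP, and DDi levels during the perioperative period". For the factors it has "Changes of the plasma II, VII, IX, X, XI, and XII levels during the perioperative period". It gives neither a reference time nor a measure of change.

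*Objective.* Objective and hypothesis states the main purpose as being to "determine if the levels of pro-inflammatory cytokines and anti-inflammatory cytokines differ between the two study groups".

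*Samples.* Blood sample collection and detection starts the inflammatory-factor schedule at "before operation (T0), CPB initiation (T1), lowest intraoperative temperature (T2") and runs it to T7 at 72 h. The clotting tests are taken "before operation, 24 h after completion of the procedure (POD 1), 48 h after completion of the procedure (POD 2), and 72 h" (POD 3). The coagulation factors also have a preoperative sample.

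*Analysis.* Data analysis states: "Levels of inflammatory cytokines and coagulation parameters will be expressed as mean ± standard deviation or median (interquartile range"). The next sentence names an independent t test or Wilcoxon signed-rank test and gives it the task of checking normality. A method for change over time appears only in the sentence that begins "When comparing the changes in coagulation factor levels during the perioperative period"; it names repeated-measures ANOVA and ANCOVA, without a covariate. The other methods, assigned to primary and secondary outcomes in general, are logistic regression, Kaplan-Meier curves and the log-rank test.

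**The concern.** The sampling section separates clotting tests (its coagulation parameters) from coagulation factors. Read in those terms, the longitudinal sentence covers the factors and leaves out cytokines, MIF, CRP and the clotting tests. Logistic regression and log-rank tests do not fit serial continuous measurements. That leaves these markers with a sentence about levels and a test assigned to a task it cannot do: neither test checks normality, and the signed-rank test is for paired data, not for two independent groups.

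The analyst can therefore compare levels, compare changes from the preoperative value, or adjust for that value, and cite some part of the article for the first two. These options differ in precision and can fall on different sides of p = 0.05 in the same data. Inclusion criteria admit patients up to 7 days after onset, so preoperative marker values may well vary between patients, and that is when adjustment could help. The markers are secondary outcomes, but the article calls the cytokine comparison its main purpose.

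**Working it through.** **1. The text side by side**

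| Markers | Outcome worded as | Preoperative sample | Longitudinal method stated |
|---|---|---|---|
| Cytokines, MIF, CRP | change, up to 3 days | T0 | none |
| APTT, PT, FIB, FDP, DDi | change, 3 days | yes | none |
| Factors II, VII, IX, X, XI, XII | change, 2 days | yes | repeated-measures ANOVA and ANCOVA, covariate not named |

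I take MIF and CRP to follow the inflammatory-factor schedule; the sampling section does not name them separately.

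**2. The plan's own figure**

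The only stated sample size is for the clinical composite: 40 per group, from 33.3% (4/12) against 8.3% (1/12), two-sided α 5%, power 80%. The pooled formula has mean proportion 0.2083:

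n = [1.96·√(2 × 0.2083 × 0.7917) + 0.8416·√(0.2222 + 0.0764)]² / 0.25² = (1.1257 + 0.4599)² / 0.0625 = 40.2, so 41.

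This agrees closely with 40 and is untouched by the present point. The article gives no SD, effect size or correlation for the laboratory markers, so what follows rests on assumptions.

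**3. Precision of the three options**

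Let ρ be the within-arm correlation between the preoperative and a follow-up value, and k the ratio of preoperative SD to follow-up SD. Per time point, relative to the variance of a level comparison:

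- change: 1 + k² − 2ρk, which is 2(1 − ρ) when k = 1
- level adjusted for the preoperative value (ANCOVA): 1 − ρ²

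Power uses n = 40 per arm and an assumed true difference of 0.5 SD: Φ(0.5 / (√v × √(2/40)) − 1.96), where v is the relative variance and √(2/40) = 0.224. With k = 1:

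| ρ (assumed) | v, change | v, ANCOVA | Power: level | Power: change | Power: ANCOVA |
|---|---|---|---|---|---|
| 0.3 | 1.40 | 0.91 | 61% | 47% | 65% |
| 0.5 | 1.00 | 0.75 | 61% | 61% | 73% |
| 0.7 | 0.60 | 0.51 | 61% | 82% | 88% |

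The equal-variance assumption matters mainly for the change column. With k = 1/3 (follow-up SD three times the preoperative SD, also assumed), change gives 1 + 1/9 − 2ρ/3 = 0.91, 0.78 and 0.64 at ρ = 0.3, 0.5 and 0.7. The difference between change and ANCOVA is (1 + k² − 2ρk) − (1 − ρ²) = (k − ρ)², which is never negative. So, apart from the degree of freedom spent on the slope, ANCOVA is at least as precise as either alternative at any k.

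**4. How often level and change disagree**

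Simulation of 20,000 trials per setting, 40 per arm, k = 1, one marker at one time:

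| ρ | Disagree on p < 0.05, 0.5 SD effect | Disagree, no effect | Type I error: level | Type I error: change |
|---|---|---|---|---|
| 0.2 | 31.5% | 7.3% | 5.2% | 4.9% |
| 0.5 | 32.3% | 8.3% | 5.3% | 5.0% |
| 0.8 | 38.8% | 9.0% | 5.3% | 4.9% |

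Either test, fixed in advance, holds its error near 5%. With no effect, the chance that at least one is significant is (level + change + disagreement)/2. At ρ = 0.2 that is (5.17 + 4.94 + 7.29)/2 = 8.7%; at ρ = 0.8 it is (5.27 + 4.90 + 9.02)/2 = 9.6%.

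**The case against.** The strongest reply is that the article contradicts itself less than it seems to. Changes in levels over the perioperative period may simply mean the course over repeated samples, which is how Data analysis uses the phrase for coagulation factors. No subtracted change score is defined anywhere. The objective is a general statement of purpose. Which model each secondary marker gets is commonly left to a full protocol or analysis plan, and neither is shown. Under randomization each option is a valid test, and the size of any gain rests on assumed values.

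Much of this stands. Silence on model detail would be no finding, and there is no bias. But the article is not merely silent: it sets out methods for its outcomes, ties the only suitable one to a single marker group, and gives the others a test described as something it is not. If change does mean the course over time, the cytokines and clotting tests need that longitudinal analysis just as the factors do.

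A reader might go further and infer that the plan compares unadjusted levels and discards the T0 sample. The documents do not support that. The text says only how levels will be summarised and assigns the t test or Wilcoxon test to a normality check. Nothing says T0 is left out; an outcome worded as a change would naturally use it, and Data management and quality control plans multiple imputation for unusable preoperative samples. Nor can one infer that the coagulation factors are already adjusted for their preoperative value, since no covariate is named.

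**Conclusion.** The point holds as an inconsistency and a missed gain in precision. Outcomes worded as changes, an objective and analysis worded as levels, and a longitudinal analysis confined to coagulation factors leave the choice between level and change open for the cytokines, MIF, CRP and clotting tests.

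Under the stated assumptions, adjustment for the preoperative value would cut the variance of a level comparison by 9%, 25% or 49% at ρ = 0.3, 0.5 or 0.7. At the low end the gain is small (power 61% to 65% for a 0.5 SD difference). Correlation, effect size and equal variances are assumptions, and the comparison with change scores is sensitive to the last. The error rate of 8.7% to 9.6% arises only if the more favourable of two analyses is picked after the data are seen; nothing in the article says that this would be done. The primary composite and its sample size are unaffected.

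**What to change.** - In Secondary outcome measures and Data analysis, define each cytokine, MIF, CRP and clotting-test outcome in the same way: the between-arm difference in level at named times after T0, on the log scale where values are skewed, adjusted for the patient's own preoperative value. Word the objective to match.
- Extend the repeated-measures/ANCOVA model to these markers, keep it for the coagulation factors, and name the preoperative value as the covariate for all of them.
- Reword the t test/Wilcoxon sentence so that it no longer presents these tests as a check of normality.
- State how the model treats an unusable preoperative sample, consistently with the multiple imputation in Data management and quality control.

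The cost is a few lines of text. The preoperative samples are already scheduled, so no visit, assay or patient is added. The choice should be fixed before the allocation is linked to the laboratory results.

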### Other outcome measures

The volume of blood transfusion within ICU [time frame: up to 30 days]The need of vasoactive drugs [time frame: up to 30 days]Length of ICU stay [time frame: up to 30 days]Length of postoperative hospital stay [time frame: up to 30 days]Prolonged postoperative extubation (> 48 h) [time frame: up to 30 days]Total hospital expenses [time frame: up to 6 months]

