### Data collection using case report form (CRF)

Preoperative data including preoperative demographics (sex, age, BMI), details of presentation (onset time, symptoms such as chest pain, back pain, dyspnea, abdominal pain/abdominal distension, nausea/vomiting, coma, etc.), prior medical history (hypertension, hyperlipidemia, diabetes, coronary heart disease, kidney disease, cerebrovascular disease, smoking history, drinking history, etc.), preoperative imaging and laboratory results (such as electrocardiogram, cardiac ultrasound, computed tomography angiography, coagulation routine, liver and kidney functions, blood routine, etc.), and preoperative medications (norepinephrine, dopamine, urapidil, epinephrine, etc.) will be collected.

Intraoperative data including surgical methods, CPB details (CPB time, aortic cross-clamp time, circulatory arrest time, unilateral cerebral perfusion time, nasopharyngeal minimum temperature, etc.), volume of intraoperative blood products (such as suspended red blood cells, fresh frozen plasma, platelet, cryoprecipitate, etc.), amount of blood loss, and urine output will also be collected.

Postoperative follow-up data including major postoperative complications (new renal failure-requiring dialysis, secondary thoracotomy, operative mortality, stroke/cerebrovascular accident, paraplegia, acute renal injury, respiratory failure, delirium, severe liver dysfunction, myocardial infarction, etc.), general condition after operation (duration of mechanical ventilation, drainage volume within 24 h postoperatively, urine volume within 24 h postoperatively, the length of ICU stay, all-cause mortality, dosage of vasoactive drugs, total hospitalization cost, etc.), and volume of postoperative blood product transfusions will be collected. Utilization of invasive postoperative treatment methods such as continuous renal replacement therapy (CRRT) or extracorporeal membrane oxygenation (ECMO) will be documented as well. In general, all patients enrolled will be followed up at our center. Part of the data to be collected throughout the study is shown in Fig. 3.

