Our study will also aim to evaluate the changes of postoperative blood coagulation function and determine the new mechanisms of postoperative organ failure. Macrophage migration inhibitory factor (MIF) is a secretory homotrimer that plays a key role in promoting the production of proinflammatory cytokines [35–37]. With a molecular weight of 12.5 kD, MIF can be effectively removed by the HA380 hemoperfusion. Removal of MIF may have a protective effect on the central nervous system and reduce the incidence of postoperative delirium. Further, free hemoglobin and myoglobin can also be readily removed by the HA380 hemoperfutor during CPB. Because both hemoglobin and myoglobin are involved in the occurrence of cardiac surgery-associated acute kidney injury (CSA-AKI) [38], hemoperfusion may have an additional protective effect on the kidney and may contribute to the recovery of renal function after cardiac surgery.

Because the interplay between inflammation and coagulation systems seriously worsens the prognosis of patients undergoing surgery, we therefore aim to evaluate if hemoperfusion could reduce abnormal bleeding and the amount of transfusion after the aortic arch operation. Additionally, in order to evaluate the safety of HA380 hemoperfutor, we will also detect the levels of perioperative coagulation factors such as II, VII, IX, X, XI, XII, and so on.

Steroids are commonly used for the excessive inflammation in ATAAD patients with severe postoperative inflammation [39]. While effective, steroid uses are not without side effects. Hyperglycemia and increased risk of postoperative infection are common side effects seen with steroids. Another anti-inflammatory drug, ulinastatin, can cause granulocytopenia and allergies. Therefore, other emerging technologies such as hemofiltration are needed to address the limitations of medications. Though well tolerated, one limitation with the hemoperfusion technologies is the inconsistent filtration and adsorption results.

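### The transfusion outcome counts only products given in ICU, so it cannot tell a true saving from a shift of products into the operating room

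*Protocol article*

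**What the plan says.** - **Transfusion outcome.** Protocol article, Other outcome measures: "The volume of blood transfusion within ICU [time frame: up to 30 days". Objective and hypothesis uses the same scope: "blood product usages in the intensive care unit (ICU".
- **What is recorded.** Data collection using case report form (CRF) includes the "volume of intraoperative blood products (such as suspended red blood cells, fresh frozen plasma, platelet, cryoprecipitate, etc.), amount of blood loss". It also collects postoperative transfusion volume, not limited to ICU. Intraoperative products and intraoperative blood loss appear in none of the primary, secondary or other outcome lists.
- **Clotting tests.** Under Blood sample collection and detection, APTT, PT, fibrinogen, FDP and D-dimer are measured "before operation, 24 h after completion of the procedure (POD 1), 48 h after completion of the procedure (POD 2), and 72 h".
- **Clotting factors.** The same section schedules factors II, VII, IX, X, XI and XII at "before operation, end of CPB, end of the operation, 24 h after completion of the procedure (POD 1" and again at 48 h.
- **Declared safety measure.** The Discussion states that "in order to evaluate the safety of HA380 hemoperfutor, we will also detect the levels of perioperative coagulation factors". It also says that the trial will examine whether hemoperfusion reduces abnormal bleeding and transfusion after the operation.

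**The concern.** The device can act on the patient only while bypass is running. Any effect on clotting, good or bad, should first show between the end of bypass and chest closure. That is when the surgical team works to reach hemostasis and when blood products may be given. The listed transfusion outcome starts after that window.

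If one group receives more products in theatre, it may arrive in ICU already replaced and need less there. The ICU volume would then favor that group although its total use was no lower, or was higher. The reverse also holds: a saving made in theatre would be missed. At stake is the trial's statement on transfusion and, to a lesser degree, the reading of its coagulation results, since products given earlier can alter later samples and the 24 h drainage.

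**Working it through.** The plan gives no transfusion figure to reproduce. Its sample size rests on the composite of major complications and plays no part here. The check is a comparison of windows, followed by a short illustration.

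**Step 1. When the device acts.** Experimental intervention/treatment and the Fig. 2 legend place the cartridge in the bypass circuit, taking blood after the oxygenator and returning it to the venous reservoir. Exposure therefore ends with bypass. Under Anesthesia and surgical procedures, weaning is followed by protamine if needed, then hemostasis, then closure of the sternum.

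**Step 2. What is sampled around that window.**

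| Measure | Before operation | End of CPB | End of operation | 24 h | 48 h | 72 h |
|---|---|---|---|---|---|---|
| Factors II, VII, IX, X, XI, XII | yes | yes | yes | yes | yes | no |
| APTT, PT, FIB, FDP, D-dimer | yes | no | no | yes | yes | yes |

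Post-baseline samples up to the end of the operation: 2 for the factors, 0 for the clotting tests. The end-of-CPB factor sample comes before the post-bypass period of replacement, so it is the one least affected by it. Samples from the end of the operation onward may reflect plasma or cryoprecipitate already given.

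**Step 3. Which volumes are outcomes.**

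| Volume | On the CRF | In an outcome list |
|---|---|---|
| Intraoperative products | yes | no |
| Intraoperative blood loss | yes | no |
| ICU products | yes, within postoperative transfusion | yes (other) |
| 24 h drainage | yes | yes (secondary) |

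**Step 4. How far the ICU part can mislead.** Write the between-group difference (device minus control) as

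total difference = theatre difference + ICU difference.

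The outcome reports only the second term. The total changes sign relative to it once the theatre difference is larger in size and opposite in direction.

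Assume 2 units in ICU with the device and 4 in control, and 4 units in theatre in control. None of these volumes comes from the documents. The ICU difference is 2 − 4 = −2 units, or −2/4 = −50%, in every row.

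| Theatre difference (assumed) | Device total | Control total | Total difference |
|---|---|---|---|
| 0 | 4 + 2 = 6 | 4 + 4 = 8 | −2/8 = −25% |
| +2 | 6 + 2 = 8 | 8 | 0% |
| +4 | 8 + 2 = 10 | 8 | +2/8 = +25% |

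The same ICU result is thus compatible with a saving, no difference, or an excess. The rows show what is arithmetically possible, not what is likely.

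**The case against.** The strongest reply is that the intraoperative period is far from unobserved. Six coagulation factors are measured at the end of bypass and at the end of the operation. They are a secondary outcome and the declared safety measure. Intraoperative products and blood loss are on the CRF, adverse events are recorded with severity, secondary thoracotomy is in the primary composite, and 24 h drainage is a secondary outcome. A reader might infer from the ICU-only count and the 24 h gap in PT, APTT and fibrinogen that a coagulation harm treated in theatre would be invisible. The documents do not support that, chiefly because of the end-of-CPB factor sample. What remains is narrower: this panel lacks fibrinogen and the global clotting times.

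Other replies:

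- **The ICU scope is consistent.** The objective and the outcome list agree, and the Discussion speaks of transfusion after the operation. This stands: it is a design choice, not a contradiction. Consistency does not make the measure able to separate a saving from a shift.
- **It is a low-tier outcome**, and nowhere does the article say that ICU transfusion demonstrates device safety. This stands and limits the weight of the point.
- **The article is condensed.** A fuller protocol or an SAP may already compare intraoperative products, and the Fig. 3 schedule is not shown. This stands in part: the absence of such an analysis is not the finding. The outcome's location and the sampling times are stated in the text, and an SAP cannot create samples that were not scheduled.
- **Spare plasma is not documented.** Storage at −80 °C is described under cytokine measurement, with no statement that enough suitable plasma remains for further clotting tests. This stands.

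**Conclusion.** The point holds as an inexpensive improvement to a stated outcome window. The ICU-only volume omits every product given in theatre, although the device acts only during bypass and hemostasis is reached before closure. By itself it cannot support a claim that the device saves blood products. The size cannot be derived from the documents; the illustration shows only that a 50% ICU saving can sit beside a total anywhere from 25% lower to 25% higher under assumed volumes.

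The coagulation part is secondary. An effect can be detected through the factor panel at the end of bypass. Fibrinogen, PT and APTT have no value between baseline and 24 h, and results from the end of the operation onward are hard to read without the products given before them. Nothing in the documents indicates that the device does worsen clotting. The primary outcome is unaffected.

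The conclusion assumes that products are given in theatre in more than trivial amounts, and that this may differ between groups. The article states neither, though it provides for recording the volumes.

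**What to change.** Before unblinding:

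1. Define the transfusion outcome as total red cells, plasma, platelets and cryoprecipitate, intraoperative plus ICU up to 30 days, by product, with the intraoperative and ICU parts shown separately.
2. Add a between-group comparison of intraoperative blood loss.
3. Report coagulation results from the end of the operation onward beside the intraoperative plasma and cryoprecipitate volumes.
4. Optional: run fibrinogen and PT on the end-of-CPB and end-of-operation draws, only if suitable plasma remains.

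Items 1 to 3 change wording and tables only, since the data are already on the CRF. They remain feasible although recruitment was due to finish on 30 December 2020, about five weeks after publication on 23 November 2020. Item 4 costs additional assays and may no longer be possible. The downside of item 1 is noise: the total includes surgical blood loss unrelated to the device, which is why the ICU part is kept as a component. Intraoperative data are collected by perfusionists, who know the allocation, and by anesthesiologists, who do not; where both record products, the anesthesiologists' record is the safer source.

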**Methods:**

This study is a single-center, randomized, controlled, double-blind clinical trial. The study aims to recruit 88 patients with ATAAD and aortic arch involvement who will undergo CPB and DHCA to repair the dissected aorta. Patients will be randomized equally into the CPB/DHCA only group (control group) and the CPB/DHCA + HA380 hemoperfusion group (intervention group), with 44 patients each. Patients in the control group will undergo CPB and DHCA only, while patients in the intervention group will undergo continuous hemoperfusion with HA380, in addition to CPB and DHCA. The primary outcome is a composite of major perioperative complications. The secondary outcomes include related inflammatory markers, coagulation parameters, and minor perioperative complications. To comprehensively evaluate the effect of hemoperfusion on the perioperative outcomes, we will also determine if there are differences in perioperative all-cause mortality, length of ICU stay, and total hospitalization costs.

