### Experimental intervention/treatment

Hemoperfusion is achieved through blood filtration with a hemoperfusion device named HA380 (Zhuhai Jafron Biomedical, China). The hemoperfusion device, composed of multiple parallel macroporous adsorption resin cartridges, is connected in parallel to the oxygenator and blood reservoir and perfused at a rate of 400–700 ml/min (Fig. 2). Thanks to the large medium and macroporous structure and high specific surface area, HA380 is able to adsorb superfluous inflammatory factors and excess metabolites in the blood through different forces. The outbreak of inflammatory factors is thus expected to be controlled. The aim of hemoperfusion is to decrease inflammatory mediators produced during cardiopulmonary bypass through adsorption. The ultimate goal of hemoperfusion is to decrease postoperative complications, improve postoperative recovery, and shorten the length of hospital stay. Montin et al. detailed the safety and effectiveness of HA380. General recommendations of HA380 in cardiac surgery have also been made [16].

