### Primary outcome measures

Incidence of composite major complications [time frame: up to 30 days]:
Operative mortalitySecondary thoracotomyNew onset of postoperative renal failure requiring dialysis: increase in serum creatinine value ≥ 300% from baseline or an absolute serum creatinine ≥ 354 μmol/l with an increase ≥ 44 μmol/l from baseline (KDIGO stage 3) [17]. Any patient who received acute dialysis is put into this category. Patients who have received dialysis within 1 month prior to the surgery are not eligible for this endpointParaplegiaStroke/cerebrovascular accidentsLow cardiac output syndrome: cardiac index < 2.0 l min^−1^ m^−2^ for > 8 h after surgery, regardless of treatment [18]ReintubationSevere liver dysfunction: ALT level above 500 U/l or a total bilirubin above 3.0 mg/dl [19, 20]ECMO supportMultiple organ dysfunction syndrome (MODS)

Each of these outcomes will be analyzed as a secondary endpoint.

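### ICU and hospital stay are defined as plain lengths to day 30 with no visible rule for stays ended by death, so an early death would count as a short, apparently good stay.

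*Protocol article*

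**What the plan says.** The Other outcome measures section of the protocol article lists "Length of ICU stay [time frame: up to 30 days" and "Length of postoperative hospital stay [time frame: up to 30 days", each closing its bracket there. Neither entry says how a stay ended by death is counted, and no other section does.

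The article does commit to comparing the arms. The Methods part of the abstract says that "we will also determine if there are differences in perioperative all-cause mortality, length of ICU stay, and total hospitalization costs". Objective and hypothesis says the same of length of hospital stay and all-cause mortality. Experimental intervention/treatment gives the direction for hospital stay: "The ultimate goal of hemoperfusion is to decrease postoperative complications, improve postoperative recovery, and shorten the length of hospital stay".

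Death is an outcome in the same window. Operative mortality is the first component of the 30-day primary composite, and that section adds: "Each of these outcomes will be analyzed as a secondary endpoint".

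Data analysis names no method for the stays. Its t test and Wilcoxon sentence follows the cytokine and coagulation levels, and its Kaplan-Meier and log-rank sentence covers primary and secondary outcomes only.

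**The concern.** Length of stay is read as shorter is better, but a stay can be short because the patient recovered or because the patient died. On a plain length the two look alike, and a death on day 2 gives a stay of 2 days. The weakness lies in the outcome variable itself, so the choice of test does not remove it.

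If the device prevented early deaths, the patients it saved would add long stays to its arm and the plain length would count against it. If it caused early deaths, the plain length would flatter it. Leaving out the patients who died is no remedy, because survivors are selected after randomisation and the comparison is then no longer the randomised one.

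**Working it through.** The plan gives no figure on this point to reproduce: no mortality rate, no stay distribution, and no count of deaths within the pilot events. All figures below are therefore illustrative, except the 40 patients per arm from Sample size calculation.

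**Step 1. Arithmetic on the mean.** Assume that survivors stay L = 8 days in ICU in both arms and that deaths occur in ICU on day d = 3 on average. Let m be 30-day mortality.

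Mean raw stay = m × d + (1 − m) × L:
- m = 5%: 0.05 × 3 + 0.95 × 8 = 7.75 days
- m = 10%: 0.10 × 3 + 0.90 × 8 = 7.50 days
- m = 15%: 0.15 × 3 + 0.85 × 8 = 7.25 days

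The gap between arms is (difference in m) × (L − d). At 10% v 5% it is 0.05 × 5 = 0.25 day, and at 15% v 5% it is 0.10 × 5 = 0.5 day. Both favour the arm with more deaths.

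Mean ICU-free days to day 30, death scored 0 = (1 − m) × (30 − L):
- m = 5%: 0.95 × 22 = 20.9 days
- m = 10%: 0.90 × 22 = 19.8 days
- m = 15%: 0.85 × 22 = 18.7 days

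The arm with more deaths is now worse, by 1.1 days (10% v 5%) or 2.2 days (15% v 5%).

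**Step 2. Simulation with a skewed stay.** Assume that the stay without death has the same distribution in both arms: lognormal, median 6 days, sigma 0.7, capped at 30 days. Deaths fall uniformly on days 0.5 to 5. Medians and means come from 400,000 simulated patients per arm. The last column comes from 3,000 trials of 40 per arm with a Mann-Whitney test; it is the chance of p < 0.05 with the shorter raw median in the HA380 arm.

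| Mortality, control / HA380 | Raw median (days) | Median, death = 30 (days) | Mean ICU-free days | Significant raw result for HA380 |
|---|---|---|---|---|
| 10% / 10% | 5.44 / 5.45 | 6.61 / 6.64 | 20.20 / 20.18 | 2.6% |
| 5% / 10% | 5.73 / 5.44 | 6.28 / 6.62 | 21.30 / 20.19 | 5.3% |
| 5% / 15% | 5.73 / 5.13 | 6.28 / 7.01 | 21.31 / 19.07 | 8.5% |
| 10% / 20% | 5.44 / 4.84 | 6.62 / 7.49 | 20.19 / 17.94 | 7.8% |
| 10% / 25% | 5.44 / 4.60 | 6.61 / 8.10 | 20.20 / 16.83 | 13.1% |
| 20% / 10% | 4.84 / 5.44 | 7.49 / 6.61 | 17.96 / 20.21 | 0.6% |

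In every row with unequal mortality, the arm with more deaths has the shorter raw median, by about 0.3 to 0.8 day, although the underlying stay is the same. Scoring death as the worst value, or using ICU-free days, reverses the direction each time. The last row shows the bias running against HA380 when more control patients die.

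**The case against.** The strongest reply is that the article fixes only an outcome name and a time window. It names no test for these outcomes, and the handling of deaths may sit in the full protocol or SAP, neither of which is shown. A reader might infer that raw lengths will be tested between arms. The documents do not say so; they support only that the outcomes are defined as lengths and that differences between arms will be determined. The reply does not dispose of the point, because the variable as written gives a good value to an early death.

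Other stronger readings also fail:
- **Mortality is expected to differ.** Sample size calculation expects the composite to fall. It names death as one of three kinds of pilot control event and gives no death count. Mortality may differ; no expectation is stated.
- **All these outcomes are presented as benefits.** Only hospital stay is named as a goal. ICU stay appears neutrally, among differences to be determined.
- **Hospital cost has the same defect.** Cost has a 6-month window, spending on a patient who dies is real spending, and nothing in the document shows that a fatal course is cheap.
- **A harmful device would pass unnoticed.** Operative mortality is in the primary composite and is also analysed alone, the abstract lists all-cause mortality beside ICU stay, and a safety committee monitors deaths.

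It is also fair to say that if HA380 reduces early deaths, the bias is conservative for the device, and that in the scenarios with more HA380 deaths a significant misleading result stayed uncommon, at 5% to 13%.

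**Conclusion.** The point holds as a weakness in how two outcomes are defined. As written, stays ended by early death would count among the best values, and the comparison could be biased towards either arm if early mortality differs. With equal mortality of similar timing, no difference between arms arises.

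The true size cannot be derived from the article. The illustrative range is 0.25 to 0.5 day in the mean at 10% to 15% v 5% mortality. It rests on assumed survivor stay, timing of death and mortality, and would shrink if deaths came later in the stay. The stays are listed as other outcomes, so the primary analysis and the sample size are untouched. This is a cheap improvement of low severity.

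**What to change.** Make ICU-free days and days alive and out of hospital to day 30 the between-arm comparison, with death by day 30 scored 0, using the Wilcoxon rank-sum test. Show raw ICU and hospital stay descriptively by survival status, beside 30-day mortality. Write the rule down before the allocation is revealed.

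The cost is one derived variable for each outcome. It needs only stay length and 30-day vital status; the data collection section already lists ICU stay and all-cause mortality, hospital stay is itself an outcome, and operative mortality is part of the 30-day composite. The downside is that the scale mixes survival with stay, and a patient still in hospital at day 30 also scores 0. Showing the components alongside lets the reader see which one drives a difference.
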